#### 2.6.3. Randomization and blinding

Subjects will be assigned to one of the treatment methods at a ratio of 1:1 by dynamic allocation according to a web-based registration program system (REDCap) based on the baseline factors for treatment allocation, including the type of biliary obstruction (Bismuth type IIIa or IV) and chemotherapy (planned or not). The registration secretariat will strictly control the program to prevent leakage of the assignment information to other involved personnel. Blinding will not be used in this study.

### 2.7. Study procedure

For effective drainage of the liver volume, atrophic liver and dominant right or left portal vein occlusion sites with or without liver atrophy will be avoided as much as possible. While waiting for pathological confirmation and a decision on operability, temporary biliary decompression by percutaneous drainage, nasobiliary catheters or plastic stents (PSs) is allowed until 8 weeks.

All patients will undergo ERCP using a standard duodenal scope (TJF-290, TJF-260, or JF-260V; Olympus Optical Co, Ltd., Tokyo, Japan). The procedure will be performed with the patient in a prone or semi-prone position under conscious sedation using intravenous anesthetic in the endoscopy room. This study will use the Zeo stent V (Zeon Medical Inc., Tokyo, Japan). In bilateral drainage, two SEMSs will be placed at the LHD and the a-RHD or p-RHD depending on the liver volume on CT. In trisegmental drainage three SEMSs will be placed at the LHD, a-RHD, and p-RHD. In all patients stent deployment will be performed with the partial stent-in-stent (PSIS) method using SEMSs of 10 mm in diameter. The lengths of SEMSs were 4, 6, 8, and 10 cm, depending on the length of the stricture. Endoscopic sphincterotomy will be performed depending on the operator, and all SEMSs will be placed above the papilla.

For reintervention, after confirming the cause of RBO, 6-7F PSs or SEMSs (company not specified) are inserted into each lumen of the previously deployed SEMS.

### 2.8. Follow-up

Follow-up examinations are scheduled for at least 3, 6, 12 months and every 1 year to evaluate the general condition of the patient, and perform blood testing. Patients who receive chemotherapy will be followed-up basically every 1 to 2 weeks. The study will end 6 months after the registration of the last patient. If the patient is unable to attend hospital, follow-up will be conducted over the phone. If follow-up information cannot be obtained, the patient will be considered ne lost to follow-up.

### 2.9. Sample size calculation

The primary endpoint of this study is the stent non-RBO rate. According to the results of our past study,^[9]^ the non-RBO rate of the bilateral drainage group was 72.3% with a 95% confidence interval: CI 55.8% to 84.9%. The non-RBO rate of the trisegmental drainage group was 52.9% with a 95% CI 42.4% to 63.2%. Based on this, the expected value of the non-RBO rate of bilateral drainage group is set at 72.3%, and that of trisegmental drainage group is set at 52.9%. We set the non-inferiority margin as 10%. Assuming testing with a one-sided α value of 0.05 using the exact method assuming a binomial distribution under the above set values, 33 cases are required for detection with a statistical power of 80%. Considering the exclusion/dropout rate of about 15%, the target number of cases is set at 76 cases.

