### 2.10. Statistical analysis

The full analysis set (FAS) was defined as all randomized cases excluding minimally excludable cases. Minimally excludable cases were defined as follows: Ineligible subjects who were incorrectly enrolled, cases in which the drainage treatment itself was not performed after allocation, cases in which all post-assignment outcome data are missing, and cases in which consent is withdrawn. The population of the FAS who complete treatment is defined as the per protocol set (PPS). This includes cases in which the treatment complies with the allocation, without missing data, and without serious protocol violations.

Intention-to-treat (ITT) and per-protocol (PP) methods are used for the analysis. The ITT analysis is the main analysis based on the FAS, whereas the PP analysis is a sub-analysis based on the PPS. Demographic and clinical characteristics will be presented as the median (interquartile range) for continuous variables and frequency (percentage) for categorical variables. Welch’s *t* test and a χ^2^ test will be used to compare continuous and categorical variables, respectively.

The primary endpoint analysis will be performed according to the ITT principle. A point estimate of the difference between the non-RBO proportion in the bilateral drainage group and the trisegmental drainage group and its 95% Wald confidence interval will be calculated. Non-inferiority is considered statistically significant when the lower limit of 95% CI exceeds the non-inferiority margin of 10%, or when the *P* value is less than 5%.

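### The sample size uses one-sided alpha 0.05, but the primary decision rule pairs a 95% CI with an alternative P < 5% of unstated sidedness, so the 80% power holds on one reading only

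*Protocol article*

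**What the plan says.** Section 2.9 (Sample size calculation) sets the planning values: "the expected value of the non-RBO rate of bilateral drainage group is set at 72.3" percent, "that of trisegmental drainage group is set at 52.9" percent, and "We set the non-inferiority margin as 10" percent. The test behind the calculation is described as "Assuming testing with a one-sided α value of 0.05 using the exact method assuming a binomial distribution", and the result is that "33 cases are required for detection with a statistical power of 80" percent. The total follows: "Considering the exclusion/dropout rate of about 15%, the target number of cases is set at 76 cases". With 1:1 allocation and a total of 76, the 33 can only be per arm (66 evaluable, 76 randomised), although the text does not say so.

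Section 2.10 (Statistical analysis) takes the difference in non-RBO proportions, and "its 95% Wald confidence interval will be calculated". It then gives two routes to success joined by *or*: the lower 95% limit clears the margin, or a P value falls below 5%. The sidedness of that P value is not given. The general statement at the end of section 2.10 sets a 5% significance level, also without sidedness. The abstract writes the margin as minus 10%; sections 2.9 and 2.10 write it without the sign.

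**The concern.** The lower limit of a two-sided 95% interval is a one-sided test at 0.025. The interval that matches one-sided 0.05 is a two-sided 90% interval. So the alpha used to size the trial is not the alpha of the first success criterion. The second criterion may match section 2.9 or may not, depending on a sidedness that the article does not state.

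This is the confirmatory decision of the trial. On one reading, the chance of missing true non-inferiority under the sponsor's own rates is about 29% rather than 20%. On the other, the nominal false-positive rate is 5% one-sided, twice what the reported 95% interval implies. With the two routes joined by *or* in an unblinded trial, the criterion could also be chosen once the data are known.

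**Working it through.** **Inputs**, all from section 2.9 unless noted: bilateral rate 0.723; trisegmental rate 0.529; margin 0.10; one-sided alpha 0.05; power 0.80; 1:1 allocation (section 2.6.3); 95% Wald interval (section 2.10).

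**Formulas** (normal approximation, unpooled variance):
- n per arm = (z_alpha + z_power)² × V / (d + margin)²
- power = Φ[(d + margin)/√(V/n) − z_alpha]
- V = 0.723 × 0.277 + 0.529 × 0.471 = 0.2003 + 0.2492 = 0.4494
- d + margin = 0.194 + 0.10 = 0.294, whose square is 0.0864

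**1. The plan's own figure.** One-sided 0.05: (1.645 + 0.842)² × 0.4494 / 0.0864 = 32.1, so 33 per arm. At n = 33 the standard error is √(0.4494/33) = 0.1167 and 0.294/0.1167 = 2.519. Power = Φ(2.519 − 1.645) = 80.9%. Full binomial enumeration of the Wald rule gives 79.5%. The stated figure reproduces.

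**2. The 95% interval as the rule (one-sided 0.025).**
- 33 per arm: Φ(2.519 − 1.960) = 71.2% (70.8% by enumeration).
- 38 per arm, all 76 analysed: 0.294/√(0.4494/38) = 2.703; Φ(2.703 − 1.960) = 77.1% (76.5% by enumeration).
- Size for 80%: (1.960 + 0.842)² × 0.4494 / 0.0864 = 40.8, so 41 evaluable per arm.

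**3. The two readings side by side.**

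| Governing criterion | Effective one-sided level | Power, 33 per arm | Power, 38 per arm |
|---|---|---|---|
| 95% interval, or two-sided P < 5% | 0.025 | 71.2% | 77.1% |
| One-sided P < 5% (interval redundant) | 0.05 | 80.9% | 85.5% |

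**4. Where the readings part.** With the planning standard error of 0.1167 at 33 per arm, success needs an observed difference above −0.10 + 1.645 × 0.1167 = +0.092 at one-sided 0.05, but above −0.10 + 1.960 × 0.1167 = +0.129 for the 95% interval. An observed advantage between about 9.2 and 12.9 points succeeds on one reading and fails on the other. Under the planning rates that happens in about 80.9 − 71.2 = 9.7% of trials.

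**5. Dropout allowance.** 66 × 1.15 = 75.9, so 76. Losing 15% of 76 leaves 76 × 0.85 = 64.6, below 66; dividing by 0.85 gives 66/0.85 = 77.6, so 78. The allowance that 76 supports is 1 − 66/76 = 13.2%. At 32 per arm, power is 79.8% (one-sided 0.05) or 69.9% (one-sided 0.025), so this slip is small.

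**The case against.** The strongest reply is that the only sidedness anywhere in the article is one-sided, in section 2.9. Read in that light, the P value in section 2.10 is one-sided at 5%, the *or* makes the effective level 0.05, and the power is about 80% as stated. This is a fair reading, and it means that a reader who infers that the trial simply has 71% power goes further than the document allows. The 71% is conditional on the interval, or a two-sided P, governing. But the reply does not rescue the text: on that reading the 95% interval decides nothing, and success can be claimed with its lower limit beyond the margin.

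Three further points stand. First, 33 reproduces from its stated inputs, so this is an inconsistency between sections and not an arithmetical error. Second, section 2.6.1 counts patients who die or are lost without RBO as non-RBO, so they stay in the primary analysis. Only the narrow exclusions from the full analysis set in section 2.10 reduce it, and the analysed number may be nearer 38 per arm, which puts the interval reading nearer 77%. Third, if the interval governs, the rule is stricter than planned: it costs power and does not raise the nominal false-positive rate.

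A reader might also infer from "Assuming testing with a one-sided α value of 0.05 using the exact method assuming a binomial distribution under the above set values" that 33 is wrong because an exact test needs more patients. The article does not say which exact test was used. One particular unconditional test gives 78.5% power at 33 per arm, and a gap of 1.5 points under an assumed test proves nothing.

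**Conclusion.** The inconsistency is firm: sections 2.9 and 2.10 do not share one alpha, and the either/or rule leaves the success criterion undetermined. Its size depends on the reading. With the 95% interval or a two-sided P governing, power is about 71% at 33 per arm and about 77% at 38 per arm, so even 76 patients without loss fall short of 80%. With a one-sided P governing, power is about 80%, at a one-sided error level of 5% that the reported 95% interval does not reflect. Either the power statement or the decision rule needs correcting before the data are read.

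These figures take the planning rates of 72.3% and 52.9% and a margin of −10 points as given, and read 33 as per arm. The dropout slip is real but minor.

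**What to change.** State one success criterion in section 2.10 and delete the *or*. Two versions are consistent:

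- **(a)** Keep the two-sided 95% interval (one-sided 0.025) as the sole rule, and restate section 2.9 at that level, with power about 71% at 33 per arm and about 77% at 38 per arm.
- **(b)** Keep one-sided 0.05 and make the deciding interval a two-sided 90% interval. Power of about 80% at 33 per arm then stands.

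In either case, deleting the P-value route is essential: under (a), leaving it in would make the restated 71% wrong if P is one-sided. Any P value still reported should have its sidedness given and match the interval.

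Also write the margin as −10 percentage points throughout, write 33 per arm (66 evaluable), and restate the dropout allowance as about 13%.

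The cost is wording only, with no added patients. Under (a) the published power looks less favourable. Under (b) the trial openly accepts the less strict one-sided 5% error level.

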### 2.10. Statistical analysis

The full analysis set (FAS) was defined as all randomized cases excluding minimally excludable cases. Minimally excludable cases were defined as follows: Ineligible subjects who were incorrectly enrolled, cases in which the drainage treatment itself was not performed after allocation, cases in which all post-assignment outcome data are missing, and cases in which consent is withdrawn. The population of the FAS who complete treatment is defined as the per protocol set (PPS). This includes cases in which the treatment complies with the allocation, without missing data, and without serious protocol violations.

Intention-to-treat (ITT) and per-protocol (PP) methods are used for the analysis. The ITT analysis is the main analysis based on the FAS, whereas the PP analysis is a sub-analysis based on the PPS. Demographic and clinical characteristics will be presented as the median (interquartile range) for continuous variables and frequency (percentage) for categorical variables. Welch’s *t* test and a χ^2^ test will be used to compare continuous and categorical variables, respectively.

The primary endpoint analysis will be performed according to the ITT principle. A point estimate of the difference between the non-RBO proportion in the bilateral drainage group and the trisegmental drainage group and its 95% Wald confidence interval will be calculated. Non-inferiority is considered statistically significant when the lower limit of 95% CI exceeds the non-inferiority margin of 10%, or when the *P* value is less than 5%.

Secondary endpoint analyses will be conducted to provide supplemental discussion to the results of the primary endpoint analysis. These analyses are exploratory and will not be adjusted for multiplicity, and will be conducted without considering the margin of non-inferiority. For the secondary endpoints indicated by proportions, point estimates and 95% Wald CIs of the difference between groups will be calculated. For the continuous secondary endpoints, point estimates and 95% CIs of the mean difference between groups will be calculated. Secondary endpoints indicated by categorical variables will be enumerated for each group and compared by a χ^2^ test if necessary. The survival time analysis for TRBO and overall survival will be estimated by the Kaplan–Meier method and compared by a log-rank test. Hazard ratios and their 95% Wald CIs will be obtained using the Cox proportional hazards model. The significance level is 5%, and Stata version 17 (Stata Corp. College Station, Texas) will be used to perform all statistical analyses.

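### The primary analysis does not use the two factors on which allocation is balanced; if they are prognostic, the interval is conservative and some power is lost

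*Protocol article*

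**What the plan says.** Section 2.6.3 (Randomization and blinding): "Subjects will be assigned to one of the treatment methods at a ratio of 1:1 by dynamic allocation". The balancing factors are the "type of biliary obstruction (Bismuth type IIIa or IV) and chemotherapy (planned or not").

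Section 2.10 (Statistical analysis) defines the primary analysis as "A point estimate of the difference between the non-RBO proportion in the bilateral drainage group and the trisegmental drainage group and its 95% Wald" interval, with the lower limit compared with the 10-point margin. Neither allocation factor is named and no reason for leaving them out is given.

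For time to RBO and overall survival the same section says "The survival time analysis for TRBO and overall survival will be estimated by the Kaplan–Meier method and compared by a log-rank test", and "Hazard ratios and their 95% Wald CIs will be obtained using the Cox proportional hazards model". It does not say whether either is stratified or adjusted. Of the secondary analyses as a whole it says: "These analyses are exploratory and will not be adjusted for multiplicity, and will be conducted without considering the margin of non-inferiority".

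**The concern.** The allocation and the primary analysis do not match. When arms are balanced on a factor that predicts outcome, part of the chance variation between arms is removed by design. The two-proportion Wald standard error is computed as though that variation were still present. If the factors are prognostic, the interval covers more than 95% of the time and non-inferiority is shown less often than it could be.

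This is a method the article states, not a gap. An analysis plan that adjusted for the factors would replace what section 2.10 says. The trial is small (76 planned, 33 per arm needed by its own calculation), so a few points of power are worth having if they cost little.

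**Working it through.** **1. The plan's own figure.** Section 2.9 gives rates of 72.3% (bilateral) and 52.9% (trisegmental), margin 10 points, one-sided α 0.05 and power 80%.

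- Variance sum: 0.723×0.277 + 0.529×0.471 = 0.2003 + 0.2492 = 0.4494.
- Distance from the margin: 0.194 + 0.10 = 0.294.
- n per arm = (1.645 + 0.842)² × 0.4494 / 0.294² = 32.2, so 33. This matches the stated 33, read as per arm. 66 × 1.15 = 76 matches the target.
- At 33 per arm, SE = √(0.4494/33) = 0.1167 and power = Φ(0.294/0.1167 − 1.645) = 80.9%.
- With the two-sided 95% interval of section 2.10, power = Φ(0.294/0.1167 − 1.960) = 71.2%. That drop is a separate matter. It only sets the baseline here.

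**2. What balance can remove.** With exact balance, the variance of the difference falls by the between-cell variance of the outcome rates, summed over arms and divided by n. The documents give neither prevalences nor effects, so these are assumed: prevalences 50% and 60%, and the same odds ratio (OR) for each factor. The cell weights are then 0.2 (neither factor), 0.5 (one) and 0.3 (both).

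OR 2 per factor:
- Bilateral cell rates 0.562, 0.719, 0.837 (mean 0.723). Between-cell variance = 0.2×0.161² + 0.5×0.004² + 0.3×0.114² = 0.0091.
- Trisegmental cell rates 0.345, 0.513, 0.678 (mean 0.529). Between-cell variance = 0.2×0.184² + 0.5×0.016² + 0.3×0.149² = 0.0136.
- Share removed: 0.0227/0.4494 = 5.0%. The SD falls from 0.1167 to 0.1167×√0.950 = 0.1137.

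OR 4 per factor:
- Bilateral 0.407, 0.733, 0.917: 0.2×0.316² + 0.5×0.010² + 0.3×0.194² = 0.0313.
- Trisegmental 0.199, 0.499, 0.799: 0.2×0.330² + 0.5×0.030² + 0.3×0.270² = 0.0441.
- Share removed: 0.0754/0.4494 = 16.8%. The SD falls to about 0.1065.

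**3. Simulation under dynamic allocation.** The algorithm is not given, so minimisation on the two factor margins with an 80% biased coin was assumed. At N = 66 (8,000 replicates, prevalences 50% and 60%), the unadjusted Wald analysis was compared with a main-effects linear risk-difference model with robust (HC2) standard errors:

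| OR per factor | True SD, unadjusted | Mean Wald SE | Wald coverage | Adjusted coverage | Change in width with adjustment |
|---|---|---|---|---|---|
| 1 | 0.1167 | 0.1149 | 94.2% | 94.4% | +1.7% |
| 2 | 0.1146 | 0.1149 | 94.9% | 94.5% | −1.0% |
| 3 | 0.1097 | 0.1150 | 95.8% | 94.6% | −4.4% |
| 4 | 0.1070 | 0.1150 | 96.4% | 94.6% | −7.3% |

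At OR 1.5 the adjusted interval was 0.7% wider.

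Power under the 95% interval rule, unadjusted → adjusted. The Mantel-Haenszel (MH) columns use four cells and Sato variance. OR 1 to 3 there use 6,000 replicates and prevalences 50% and 70%; the OR 4 figure is from a separate run.

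| OR | Main effects, N=66 | MH, N=66 | MH, N=76 |
|---|---|---|---|
| 1 | 70.7 → 70.0 | 70.9 → 70.4 | 76.8 → 76.0 |
| 1.5 | 71.6 → 71.6 | 71.3 → 71.3 | 76.2 → 76.0 |
| 2 | 70.5 → 71.5 | 71.0 → 72.0 | 77.7 → 78.4 |
| 3 | 72.2 → 75.4 | 71.6 → 75.2 | 77.5 → 80.8 |
| 4 | 72.9 → 78.0 | not run | 79.1 → 82.9 |

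A repeat at N = 76 gave 77.3 → 77.0 (OR 1), 77.4 → 78.0 (OR 2) and 77.0 → 80.0 (OR 3). The Monte Carlo standard error of one power figure is about √(0.7×0.3/6000) = 0.6 points, so differences of a few tenths should not be read closely.

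**4. Type I error.** At the margin (42.9% against 52.9%, N = 66, nominal one-sided 2.5%), the unadjusted rule ran at 2.5%, 2.3% and 1.8% for OR 1, 2 and 3. The main-effects model ran at 2.5%, 2.5% and 2.2%.

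**The case against.** The strongest reply is that nothing in the article shows the factors to be prognostic. Section 2.6.3 calls them only baseline factors for allocation. With no effect, adjustment slightly widens the interval. At an odds ratio of 2 for both factors it gains about one point of power, and more than about three points requires an odds ratio of at least 3 for both at once. This stands, and it makes the size conditional. Two features of the article do make an effect of chemotherapy plausible, though they give no size. Section 2.6.1 counts patients who die or are lost without RBO as non-RBO, and section 2.8 has chemotherapy patients seen every 1 to 2 weeks against scheduled visits at 3, 6 and 12 months.

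It can also be said that the unadjusted difference is a simple marginal estimate that matches the unstratified calculation in section 2.9, and that four-cell stratification is thin. At prevalences of 50% and 70%, the smallest cell-by-arm count was 4 or fewer in about 85% of simulated trials at N = 66 and 67% at N = 76. Both are fair. They bear on the choice of adjusted method and on keeping the unadjusted estimate, not on whether to adjust.

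A reader might infer that the log-rank and Cox analyses are unstratified and share the fault. The article does not say so. It is silent on strata and covariates, which an article may leave to the full plan, and it calls these analyses exploratory.

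**Conclusion.** The point holds in a conditional and modest form. As written, the primary analysis does not use the two allocation factors. If they are prognostic, the unadjusted interval is conservative and power is lost. Under the 95% interval rule with 66 to 76 patients, adjusting changes power by a loss of under one point with no effect, a gain of about 0.5 to 1 point at an odds ratio of 2 per factor, and about 3 to 5 points at odds ratios of 3 to 4. These figures rest on assumed prevalences, equal odds ratios for both factors and assumed minimisation, none of which the article gives.

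Two stronger readings are tempting and not supported. The first is that the interval is simply too wide and power is lost for nothing: with no prognostic effect the Wald interval is, if anything, slightly narrow (coverage 94.2%) and adjustment gains nothing. The second is that the non-inferiority conclusion would be invalid: as the factors' effect grows, the unadjusted rule's type I error falls below nominal, so omitting them makes no false claim of non-inferiority more likely. This is a point of efficiency and interval accuracy. It rests on the primary endpoint only, and at moderate effects it is smaller than the roughly 10 points of power between one-sided 0.05 in section 2.9 and the 95% interval in section 2.10.

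**What to change.** Make the primary estimate a risk difference adjusted for Bismuth type and planned chemotherapy, using the values entered at allocation. Suitable methods are a main-effects risk-difference model with robust standard errors, Mantel-Haenszel weights with Sato variance, or a stratified Miettinen-Nurminen interval. Because the four cells are small, the main-effects model is the safer choice of the two that were simulated: its coverage at the planning rates was 94.4 to 94.6%, against about 93 to 95% for the four-cell Sato interval. Keep the unadjusted difference as a sensitivity analysis. If the sponsor prefers it as primary, give the reason. It would also help to state whether the log-rank and Cox analyses use the two factors, though nothing here depends on that.

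The cost is a few lines of code, with both factors already recorded in the allocation system. The downside is an interval about 1 to 2% wider if the factors are not prognostic, and sparse cells if four-way stratification is chosen. The choice should be fixed before outcome data are examined.

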## 3. Discussion

Bilateral endoscopic drainage with SEMS can be used to effectively manage patients with HMBO.^[1–5]^ However, few reports have described the utility of trisegmental drainage and the benefits of using trisegmental drainage remain unknown.^[6–9]^ There have been no RCTs to compare bilateral and trisegmental drainage in patients with high-grade HMBO. The primary endpoint of this multicenter RCT is the comparison of the non-RBO rate at 6 months between bilateral and trisegmental drainage in patient with high-grade HMBO. The secondary endpoints are the rates of technical and clinical success, procedure time, procedure related AEs, TRBO, technical and the clinically successful reintervention, and overall survival in the two groups. If the non-inferiority of bilateral drainage is demonstrated, it is predicted that the procedure time will be shortened, and medical costs will be reduced.

Recent studies have reported that the technical success rate and stent patency in patients with HMBO treated with bilateral drainage using SEMS were 90% to 100% and 4.2 to 16.3 months, respectively.^[2–5]^ Only three previous studies have been published on trisegmental drainage using three SEMSs; these reported technical success rates and stent patency of 82% to 100% and 5.7 to 7.1 months, respectively.^[6–9]^ Each study was associated with some limitations, the benefit of trisegmental drainage is not clear. In our previous study, we compared stent patency between bilateral and trisegmental drainage in patients with HMBO limited to Bismuth IIIa or IV; however, the study was associated with some limitations.^[9]^ First, this was a retrospective study that included a small number of patients in the bilateral drainage group. Second, the decision to perform bilateral or trisegmental drainage was left to the discretion of each physician. Third, although most cases underwent drainage using the PSIS method, three drainage methods were utilized. Finally, various devices, SEMSs, and PSs were used.

This study will resolve the limitations of previous studies. We believe that this RCT will be able to correctly assess the study endpoints.

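### Wald intervals for secondary differences in proportions are too narrow at about 38 per arm when a rate is near 0% or 100%; a score interval is a cheap improvement

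*Protocol article*

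**What the plan says.** Section 2.10 (Statistical analysis) names the interval method twice. For the non-RBO proportion, a point estimate of the difference is given and "its 95% Wald confidence interval will be calculated". For the secondary endpoints the text reads: "For the secondary endpoints indicated by proportions, point estimates and 95% Wald CIs of the difference between groups will be calculated". No other method is named for sparse counts or for an arm at 0% or 100%. The same section calls the secondary analyses exploratory, without multiplicity adjustment and without a non-inferiority margin.

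The arms are small. Section 2.9 states that "33 cases are required for detection with a statistical power of 80"% and that "the target number of cases is set at 76 cases". Allocation is 1:1 (section 2.2), so about 38 patients per arm are planned.

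The documents also show how high one secondary proportion may be. In the Discussion, technical success and stent patency in patients "treated with bilateral drainage using SEMS were 90% to 100% and 4.2 to 16.3 months, respectively"; for trisegmental drainage the cited technical success is 82% to 100%. The Introduction gives the group's own retrospective results as 34/36 and 80/89. No adverse event rates are given.

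**The concern.** The Wald interval estimates its standard error from the observed proportions. When an arm is observed at 0% or 100%, its contribution to the variance is zero, however few patients it has. If both arms are at the same boundary, the interval collapses to a single point. Close to the boundary it does not collapse, but it is too short and its coverage falls below 95%.

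Technical success can plausibly reach that region on the article's own figures. Individual adverse event types such as perforation could do so at the other end, if they are analysed as proportions. At stake are the error bars on descriptive secondary results: a published interval of 0 to 0 would claim a certainty that 76 patients cannot give.

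**Working it through.** **Sample size behind the check.** Section 2.9 sets rates of 72.3% and 52.9%, a margin of 10 points, one-sided α of 0.05 and 80% power. With the unpooled normal approximation:

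n = (1.645 + 0.842)² × (0.723 × 0.277 + 0.529 × 0.471) / (0.723 − 0.529 + 0.10)² = 32.1, rounded up to 33 per arm.

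Then 33 × 1.15 = 37.95, so 38 per arm and 76 in total. Both stated figures are reproduced, with 33 read as a per-arm number. The check uses n = 38, with n = 33 as the smaller case.

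**Formula in the plan.** Wald: d ± 1.96 × √[p₁(1 − p₁)/n + p₂(1 − p₂)/n], where d = p₁ − p₂.

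**Intervals for given results, 38 per arm, in percentage points.**

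| Result | Wald | Newcombe | Miettinen-Nurminen |
|---|---|---|---|
| 38/38 vs 38/38 (or 0 vs 0 events) | 0.0 to 0.0 | -9.2 to 9.2 | -9.3 to 9.3 |
| 38/38 vs 37/38 | -2.5 to 7.7 | -6.8 to 13.5 | -6.8 to 13.6 |
| 38/38 vs 36/38 | -1.8 to 12.4 | -4.7 to 17.3 | -4.3 to 17.4 |
| 36/38 vs 34/38 (close to the prior rates) | -6.8 to 17.3 | -8.3 to 19.4 | -8.4 to 19.8 |

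The first row can be checked by hand. Both Wald variance terms are 1 × 0/38 = 0. The Wilson lower limit for 38/38 is 38/(38 + 1.96²) = 0.908, so the Newcombe limits are ±(1 − 0.908) = ±9.2 points.

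**Coverage.** For assumed true rates, the binomial probabilities of all pairs of counts whose interval contains the true difference are summed. Nominal coverage is 95%.

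| True rates | Wald, n = 38 | Zero width, n = 38 | Newcombe, n = 38 | Wald, n = 33 |
|---|---|---|---|---|
| 94.4% vs 89.9% (34/36, 80/89) | 95.3% | 0.2% | 97.3% | 93.5% |
| 95% vs 90% | 93.7% | 0.3% | 96.4% | 93.4% |
| 98% vs 95% | 85.2% | 6.6% | 98.9% | 81.3% |
| 100% vs 95% | 85.5% | 14.2% | 99.8% | 81.1% |
| 100% vs 90% | 89.4% | 1.8% | 97.8% | 85.2% |

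The zero-width column is the chance that both arms are at 100%: 0.98³⁸ × 0.95³⁸ = 0.464 × 0.142 = 0.066, and 1 × 0.95³⁸ = 0.142.

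The shortfall at 100% vs 90% can be traced. The Wald interval misses the true 10 points when the second arm has no failure (0.9³⁸ = 0.018) or one failure (38 × 0.1 × 0.9³⁷ = 0.077; upper limit 7.7). That is 9.5% on one side. Nine or more failures add 1.1% on the other, so coverage is 89.4%.

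**Adverse events (rates assumed).** At 38 per arm, Wald coverage is 93.7% at 5% vs 10%, 85.2% at 2% vs 5% and 76.4% at 1% vs 3%. With the same 2% in both arms, coverage is 99.4%, but the chance of a 0 to 0 interval is 21.5%.

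**Primary endpoint, for comparison.** At 72.3% vs 52.9% and 38 per arm, Wald coverage is 94.2%. The one-sided error at the −10 point margin is 2.6% to 2.8% for trisegmental rates from 0.529 to 0.70.

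**The case against.** The strongest reply is that the trial will probably not be in the bad region. The only two-arm technical success data in the article are 34/36 and 80/89, where Wald coverage is close to 95%. At 95% vs 82%, with trisegmental success at the low end of its cited range, it is 93.9% at 38 per arm. Both arms at 100% is the extreme corner of the cited ranges. This stands: the failure is conditional on rates nearer the boundary than the prior study found.

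The adverse event part rests on assumed rates and on a reading of the plan. Section 2.10 also says that categorical secondary endpoints are tabulated and compared by a χ² test if necessary, so it is not certain that each event type will receive a Wald interval. This stands too.

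The undercoverage also does not create false differences: with equal true rates, Wald covers 95.9% at 95% in both arms and 99.4% at 98%. And score intervals are not perfectly calibrated here, since Newcombe covers up to 99.8% in the table. Both are true. An interval that is somewhat too wide is still a milder fault than one of zero width.

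A reader might go further and infer that the primary non-inferiority test is unsafe, because it uses Wald while section 2.9 sized the trial "using the exact method assuming a binomial distribution". The documents do not support this. At a trisegmental rate of 0.529 the one-sided error at 38 per arm is 2.8% with Wald and 2.8% with a score test. It rises to 3.2% and 3.35% only at rates of 0.85 and 0.90, which the article does not anticipate: the prior 95% interval for that arm was 42.4% to 63.2%. Counting deaths and losses as non-RBO raises the rate, but nothing in the article shows that it would reach that level.

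Nor are the secondary proportions the stated case for the simpler procedure. The article rests that case on shorter procedure time and lower cost, once non-inferiority on RBO is shown.

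**Conclusion.** The point holds as a minor one, for the secondary proportions only. At about 38 per arm the stated Wald interval covers roughly 85% to 89% instead of 95% when technical success is 98% vs 95%, 100% vs 95% or 100% vs 90%. It is 0 to 0 when both arms sit at the same boundary, where a score interval is about ±9 points. Those success rates fall inside the article's cited ranges of 90% to 100% and 82% to 100%, but above the group's own prior rates, at which coverage is near nominal. The adverse event figures depend on assumed rates.

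The method is stated in the article, so this concerns a fixed choice and not a detail left to an analysis plan. It is a cheap improvement: the endpoints are exploratory, and neither the primary conclusion nor the sample size is affected.

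**What to change.** In the secondary-endpoint paragraph of section 2.10, replace the Wald interval for differences in proportions with a score-based one, either Miettinen-Nurminen or Newcombe, and name which. The choice should be made beforehand, because the two can disagree: for 38/38 vs 34/38, Newcombe gives -0.6 to 24.1 points and Miettinen-Nurminen 0.7 to 24.2. The primary-endpoint interval need not change on this ground.

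The cost is a change of a word or two and a standard routine. The intervals become slightly wider and somewhat conservative near 0% or 100%. No further patients or data are needed.
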